## Abstract

**Methods::**

A total of 30 healthy participants older than 20 years of age will be recruited for this study. The participants would first be administered acupuncture, following which the electric characteristics will be measured using the semiconductor analyzer Agilent B1500A/Agilent 4156C. The visual analog score (VAS) will also be rated. Thereafter, a burned moxa will be added to the acupuncture needles as a method for warm needling. The electric characteristics and VAS will be measured again. We will use the paired t-test and repeated measure two-way ANOVA to compare the electric characteristics and VAS before and after warm needling in each participant.

**Objectives::**

This protocol aims to explore the thermal effect on the electric characteristics of meridians in a warm needling model and provide a scientific explanation of TCM through the aspect of physics.

## 1. Introduction

Acupuncture has been widely used to treat various diseases and relieve pain.^[1]^ In traditional Chinese medicine (TCM) theory, there are some methods to improve the therapeutic effects of acupuncture, including manual manipulation, electroacupuncture (EA), moxibustion, or warm needling.^[1–4]^ Warm needling is a combination therapy of acupuncture and moxibustion by placing an ignited moxa on the handle of an acupuncture needle.^[5]^ This could stimulate acupoints by needling, heating, and pharmacological effect of moxa.^[4]^ It is thought that warm needling could warm meridians and improve deficiency-cold syndrome.^[6]^ Modern research has found that warm needling has effects on the immune, nervous, and endocrine systems^[7,8]^ and that it relieves pain^[5]^ and improves the range of motion of the shoulders,^[9]^ knee osteoarthritis,^[6]^ and lower urinary tract symptoms,.^[4]^ However, how the warm needling works on the meridians has not been identified yet.^[6]^

There is no definitive conclusion regarding what meridians and acupoints essentially are.^[10]^ Many researchers have been exploring several ways, including biophysics and biochemistry, to elucidate the meridians.^[11]^ Researchers explored meridians and acupoints according to the physical and electric characteristics of the human skin, and the result showed that some specific parts of the skin had the characteristic of higher conductivity, lower resistance, and higher potential.^[12,13]^ Furthermore, the researchers found that the specific parts of the skin and acupoints on the meridians were matched.^[14–16]^ Recently, some studies combined semiconductor and TCM theory to discuss the meridian phenomena and the relationship between electric characteristics and meridians.^[17,18]^ Hung et al introduced the ion current model and compared different kinds of pulses, and found that ions might be the substance delivered by the meridians.^[17]^ Wang et al applied supercritical fluid technology to discriminate the relation between different conductivity of acupuncture needles and the electric properties of the meridians. It was proven that electrical conductivity and the therapeutic effects of the meridian could be improved by supercritical fluid technology.^[18]^ Additionally, the directions of ion transport in the meridians and changing the direction of needling could influence the electricity of the meridians.^[19]^ Moreover, the change of needling direction could also affect the electric current, which implies that the acupuncture manipulations might produce different effects in humans.^[20]^

The change in the physical properties of the acupuncture needle could produce different electric characteristics in the meridians and the phenomena could be explained by physics.^[17–20]^ However, there is no published research on the relationship between temperature and electric characteristics in the meridians. The purpose of our study is to combine the theory of TCM and physics to explore the thermal effect on the electric characteristics of meridians in a warm needling model. We believe that our study can provide more scientific information about the effect of temperature on the meridians in physics.

## 2. Material and methods

### 2.1. Study design

This is a prospective and observational study that will be conducted by the Department of Chinese Medicine at the Kaohsiung Chang Gung Memorial Hospital and the Department of Physics at National Sun Yat-sen University from March 2022 to December 2022. The participants will be recruited from the students and staff at National Sun Yat-sen University. Our study will enroll 30 healthy participants in 1 group and all of them will receive both interventions, acupuncture and warm needling, and electric measurement. All personal data will be preserved in a locked closet and kept confidential until the end of the experiment when the principal investigator will disclose and analyze the results.

The participants will receive acupuncture, following which we will use a semiconductor analyzer to measure the electric characteristics and evaluate the visual analog scale (VAS) score before warm needling. Subsequently, we will place burned moxa on the acupuncture needles as our warm needling method. After the moxa burns out, we will measure the electric characteristics using the same evaluation method. We will analyze 1 meridian at a time and measure 12 meridians sequentially in this study. Therefore, all participants will undergo 12 sessions of measurements. Finally, we will compare individual electric characteristics data, before and after warm needling, on 12 meridians. The measurements will be completed in 1 day and the participants would not have to return for follow-up. The flow chart of the study design is presented in Figure 1.

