**Figure 2. F2:**
[figure not shown]
(A) Acupuncture on 2 acupoints of one meridian. (B) Perform EA and measure electric characteristics using semiconductor analyzer Agilent B1500A/Agilent 4156C; subsequently, add the burned moxa on the acupuncture needles as warm needling. EA = electroacupuncture.

We will add the burned moxa to the handle of the acupuncture needles as a method for warm needling (Fig. 2B). The moxa rolls are made with pure moxa and rolled in rice paper. The moxa rolls will be 1.2 cm in diameter, 1.5 cm long, and weigh about 0.9 g each. The moxa rolls would be obtained from the same manufacturer (MAC Co.). It will take about 5 to 10 minutes for the moxa to burn out.

The acupoints would be: Chize (LU5) and Kongzui (LU6), Shousanli (LI10) and Quchi (LI11), Zusanli (ST36) and Shangjuxu (ST37), Sanyinjiao (SP6) and yinlingquan (SP9), Shaohai (HT3) and Shenmen (HT7), Yanglao (SI6) and Xiaohai (SI8), Weizhong (BL40) and Chengshan (BL57), Taixi (KI3) and Fuliu (KI7), Quze (PC3) and Neiguan (PC6), Waiguan (SJ5) and Zhigou (SJ6), Yanglingquan (GB34) and Guangming (GB37), and Ligou (LR5) and Zhongdu (LR6). The schematic picture of acupoints lists in Figure 3. These acupoints are based on the World Health Organization standard acupuncture point locations.^[21]^

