### 2.4. Outcome measurement

The primary outcomes are the electric characteristics of each meridian measured using the semiconductor analyzer Agilent B1500A/Agilent 4156C, which has been used for meridian electricity evaluation.^[20]^ This machine integrates multiple measurements, including fundamental current-voltage (IV), capacitance-voltage, pulsed IV measurement, and analysis capabilities. The IV measurement ranges from 0.1 fA to 1 A and 0.5 µV to 200 V. The maximal pulse forcing is 40 V and the minimal sampling interval is 5 ns.^[17]^ We would adjust the output electrical parameters. Further, the voltage and current will be supplied by the semiconductor analyzer Agilent B1500A/Agilent 4156C and the electric characteristics will be measured immediately as baseline data (before warm needling) (Fig. 2B). After the moxa burns out, we will again measure the electric characteristics (after warm needling).

The secondary outcome is VAS, a tool for pain assessment. The VAS is a self-reported pain rating scale recorded between 0 and 10.^[22]^ A lower score means less pain while a higher score means more pain. VAS has been used to rate the common *De Qi* sensations subjectively, including ache, numbness, heaviness, pressure, and twinge.^[23]^ Hence, we assess the *De Qi* sensations before and after warm needling by VAS.

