According to the World Health Organization International Standard Terminologies On Traditional Medicine In The Western Pacific Region, warm needling is a practice of acupuncture in which the needle is warmed during needling by placing a burned moxa stick on the handle of the needle after insertion.^[31]^ This therapeutic technique delivers heat at acupoints to stimulate the circulation of Qi and blood. In TCM theory, this procedure achieves the effect of a warm supplement, which means to activate and restore a decreased function to normal.^[31]^ In the present study, EA, through the semiconductor analyzer Agilent B1500A/Agilent 4156C, applied the same voltage before and after warm needling. Recent meridian studies showed that the meridian has electric characteristics and physical properties.^[17]^ Additionally, improving the conductivity of the meridians could cause higher electric current and lower impedance in the meridians, which could enhance de-qi sensations and increase the therapeutic effect.^[32]^ Since there are different acupuncture manipulations in traditional Chinese theory, a previous study revealed that the electric current measured during acupuncture was significantly larger in supplementation manipulation than in draining manipulation in the meridians.^[20]^ Accordingly, we expected the changing electric characteristics to a higher current after warm needling would be comparable with the current measured before warm needling since warm needling is a supplementation method. There will be new physical discoveries of warm needling, acupuncture plus moxibustion, in our study.

Although the therapeutic effects of warm needling have been affirmed clinically, the mechanism of warm needling has not been widely elucidated. Few studies discussed the association between ionic conductivity and change of temperature in the biophysical field. This is an interdisciplinary study that has not been performed before, whereby TCM professionals cooperated with physics professionals, toward exploring warm needling using new methods and interventions. The results of electric characteristics related to warm needling will give a new perspective on this popular and effective TCM treatment. The electrical intervention and electric characteristics of warm needling are expected to have vast applications in medical treatment.

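### The one-group before/after comparison measures the change after warm needling as a whole and cannot attribute it to heat, which is the stated objective

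*Protocol article*

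**What the plan says.** The Objectives paragraph of the abstract states: "This protocol aims to explore the thermal effect on the electric characteristics of meridians in a warm needling model". The Introduction repeats this aim and promises information on how temperature acts on the meridians.

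Section 2.1 describes the design: "Our study will enroll 30 healthy participants in 1 group and all of them will receive both interventions, acupuncture and warm needling, and electric measurement". The order is the same throughout. With the needles in, "we will use a semiconductor analyzer to measure the electric characteristics and evaluate the visual analog scale (VAS) score before warm needling"; moxa is then burned on the needles; and "After the moxa burns out, we will measure the electric characteristics using the same evaluation method". The 12 meridians are taken one after another on one day, and all are heated.

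On timing, section 2.3 says of the moxa: "It will take about 5 to 10 minutes for the moxa to burn out". Section 2.4 says that, once the analyzer supplies voltage and current, "the electric characteristics will be measured immediately as baseline data". The Discussion adds that the electroacupuncture given through the analyzer "applied the same voltage before and after warm needling", so each second reading follows one earlier stimulation. Section 2.6 compares post with baseline by paired t test and two-way repeated-measures ANOVA.

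The Introduction itself names three routes by which warm needling may act: the needle, the heat and a pharmacological action of the moxa.

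**The concern.** The aim names one cause, heat, but the comparison changes several things at once. Every second reading differs from the first in four further respects: the needle has been in longer, time has passed, a stimulation has already been given, and moxa has been burned, with whatever it does besides warming. Nothing in the design varies heat while holding these fixed: there is no unheated wait, unlit moxa, unheated meridian or repeated baseline.

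What is at stake is the conclusion. The Discussion expects a higher current after warm needling because it is a supplementing technique. A rise would naturally be read as confirming this, although retention or repeated stimulation could produce it. A fall from those sources could equally hide a real effect of heat. The De Qi score on the VAS, the secondary outcome, has the same weakness.

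**Working it through.** **Inputs.** n = 30 in one group (section 2.1); power 0.8, alpha 0.05, effect size 0.53 (section 2.5); paired t test (section 2.6); about 5 to 10 minutes of burning between readings (section 2.3). Sidedness is not stated; two-sided is used because it reproduces the stated n. The size of any drift is not in the documents and is assumed.

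**1. What the paired difference contains.** Write h for heat, m for any non-thermal effect of moxa, s for the after-effect of the first stimulation, and r for the change from needle retention and time between the readings. In every session of every participant,

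post − pre = h + m + s + r + error.

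All four terms enter with coefficient 1 each time. The data determine their sum and nothing else. The ANOVA does not help: the article does not name its factors, and if the second is meridian, each of the 12 changes carries the same four terms.

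**2. The plan's own figure.** For a paired t test the noncentrality is λ = d√n, with n − 1 degrees of freedom. With d = 0.53 and n = 30, λ = 0.53 × 5.477 = 2.903; the critical value on 29 df is 2.045; power is 0.801. So 30 is reproduced. The arithmetic is sound; the question is what the test estimates.

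**3. No heat effect, some drift (illustration).** Set h = 0 and let m + s + r equal δ standard deviations of the paired difference, so that λ = δ√30.

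| δ (assumed) | λ | P(two-sided P < .05) |
|---|---|---|
| 0 | 0 | 0.050 |
| 0.1 | 0.548 | 0.083 |
| 0.2 | 1.095 | 0.185 |
| 0.3 | 1.643 | 0.355 |

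A larger sample does not help: at δ = 0.3 and n = 60, λ = 2.324 and the probability rises from 0.36 to 0.63.

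**4. Drift in the other direction (illustration).** Suppose heat truly adds the planned 0.53 SD. A drift of −0.13 leaves 0.53 − 0.13 = 0.40, and power falls from 0.80 to 0.56. A drift of −0.23 leaves 0.30, and power is 0.36.

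**5. What 0.3 SD would mean in current.** Section 2.5 gives Lung-meridian currents of 0.49 ± 0.11 and 0.38 ± 0.13. These compare two input directions, not heated with unheated, so they serve only for scale. With an assumed within-person correlation of 0.5, SD of the difference = √(0.11² + 0.13² − 2 × 0.5 × 0.11 × 0.13) = √0.0147 = 0.121. Then 0.3 SD = 0.036, or 7% of 0.49 and 10% of 0.38. Over correlations of 0.3 to 0.7 the range is 6% to 11%.

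**The case against.** The strongest reply is that the article claims little. It sets out to explore, calls itself observational, enrols healthy people, and consistently defines its comparison as before against after warm needling. One group and one order are stated openly. Part of the fixed order is also unavoidable: within a session, an unheated reading cannot follow heating without residual heat. This stands as far as it goes. The before/after change under the whole procedure can be described validly, and the real gap is the missing unheated comparator. But exploring excuses imprecision. It does not make heat estimable, and heat is what the aim names. Nor is this a detail left to an analysis plan, since no analysis plan could repair it.

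Some stronger readings are tempting but unsupported:

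- A reader might infer that retention, time and stimulation all push the same way as heat, so that the bias is always towards a false positive. The documents give no direction for any of them.
- A reader might take the word in section 2.4 about measuring at once to mean straight after needle insertion, making needle settling the dominant source of drift. In context it follows the supply of voltage and current. The interval from insertion to baseline is not stated.
- A reader might put the false-positive rate at 80%, by assuming a drift of 0.53 SD. That only restates the planned power.
- A reader might conclude that the design must be rebuilt with lit and unlit meridians. That would be a trade-off and is not required (see the fix).

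**Conclusion.** The point holds. As designed, the trial can estimate the change in electric characteristics and De Qi after warm needling as a package; it cannot attribute that change to heat. This follows from the design alone and needs no assumption about drift.

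The bias has unknown sign and size. The rates of 8%, 19% and 36% in place of 5% rest on assumed drifts of 0.1, 0.2 and 0.3 SD, a zero heat effect and a two-sided paired t test on one meridian. They show how sensitive the test is and do not estimate an error rate for this trial. The trial can go ahead and report its before/after change, but the stated objective goes beyond what that change can show.

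**What to change.** **Needed.** Restate the objective in the abstract and Introduction, and the expected conclusion in the Discussion, as the change in electric characteristics and De Qi after warm needling, and drop the attribution to heat. This costs only a change of wording.

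**Preferable in addition.** In a random 3 or 4 of each participant's 12 sessions, take a second pre-moxa reading after an unheated wait equal to the burn time, and report the post-moxa change against that drift. Costs and limits:

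- Time: 3 × 5 = 15 to 4 × 10 = 40 extra minutes per participant, with the existing equipment and an amendment.
- The added reading is one more stimulation in those sessions.
- It yields 90 to 120 drift readings in all (30 × 3 to 30 × 4), or about 7.5 to 10 per meridian if balanced. That suits a drift estimate pooled over meridians better than 12 separate ones.
- The wait comes before the moxa, so the comparison assumes similar drift in both intervals.
- Heat is still not separated from other effects of burning moxa, and the conclusion should say so.

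**Optional redesign.** Randomising 6 meridians to lit and 6 to unlit moxa in each participant would hold retention, time and repeat stimulation equal. It leaves 15 against 15 participants per meridian (power 0.29 at 0.53 SD), allows carry-over between sessions on the same day, leaves the VAS unblinded, and also does not isolate heat from burning moxa. The sponsor may weigh it, but the point does not depend on it.

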**Figure 1. F1:**
[figure not shown]
Flowchart of the study design. EA = electroacupuncture, VAS = visual analog scale.

### 2.2. Participants

The participants who are healthy, aged over 20 years, and willing to sign the informed consent will be considered eligible for the study. The exclusion criteria for this study are: aged below 20 years, pregnant or breast-feeding women, empty stomach before the study, bleeding tendency due to thrombocytopenia or platelets <20,000/µL or taking antiplatelet medicine, and consuming hypnotics or psychoactive medicines. We intend to recruit 30 participants for this study.

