### 2.3. Interventions

All the participants in our study will receive acupuncture and warm needling. The acupuncture needles will be sterile, disposable, and 40 mm in length and 0.3 mm in diameter or 25 mm in length and 0.3 mm in diameter. The acupuncture needles would be obtained from the same manufacturer (COSMOS INTERNATIONAL SUPPLIES CO., LTD.). We will perform acupuncture on 12 meridians and choose 2 acupoints in each meridian (Fig. 2A).

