### 2.7. Data monitoring

Acupuncture, EA, and warm needling are general practices in TCM. Minor adverse side effects of acupuncture and EA include minor bruising, bleeding or pain at needle insertion sites,^[24]^ nausea, sweating, and dizziness.^[25]^ Other complications include pneumothorax and septicemia. Most adverse side effects are minor, and serious complications are rare.^[25]^ The most common adverse events related to warm needling are burns, skin rash, and pain.^[7]^ Warm needling therapy has been reported as a safe method in clinical practices.^[4]^ In our study, acupuncture will be performed by qualified doctors and the acupoints we chose are at the 4 limbs. The procedure will be safe with minimal risk of serious adverse events. The device we use for EA will apply voltage from 1 to 60 V and current under 2 mA. The voltage and current are in the therapeutic range, which means that our study is safe. Additionally, we will perform warm needling, which adds moxa on acupuncture needles and introduces heat stimulation through the needles, and thick cardboard will be placed on the skin surface to prevent burning injury. If serious adverse effects of acupuncture occur, such as fainting or general weakness, the doctor will remove the acupuncture needles and stop the intervention immediately, and we will record the reason for dropping out of the study.

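### Minor safety wording: the bleeding-risk exclusion in 2.2 names only platelet-related causes, so anticoagulant users and people with non-platelet bleeding disorders are kept out only by the undefined word 'healthy'

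*Protocol article*

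**What the plan says.** Three parts of the protocol article bear on this point.

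- **Eligibility (2.2 Participants).** Inclusion is open to "The participants who are healthy, aged over 20 years", with consent. The article then sets out its exclusion criteria as a list. The bleeding item is "bleeding tendency due to thrombocytopenia or platelets <20,000/µL or taking antiplatelet medicine". The only other medicine item is "consuming hypnotics or psychoactive medicines".
- **Exposure (2.1 Study design and 2.3 Interventions).** "We will perform acupuncture on 12 meridians and choose 2 acupoints in each meridian". The needles are "40 mm in length and 0.3 mm in diameter or 25 mm in length and 0.3 mm in diameter". "The measurements will be completed in 1 day", and no return visit is planned.
- **Safety (2.7 Data monitoring).** The side effects listed for acupuncture include "minor bruising, bleeding or pain at needle insertion sites". The article relies on qualified doctors and on acupoints confined to the limbs. It adds a cardboard shield against burns, and a rule to remove the needles and stop after a serious reaction such as fainting.

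The stated objective is to explore a thermal effect and "provide a scientific explanation of TCM through the aspect of physics". No treatment benefit to the participant is claimed.

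**The concern.** The bleeding item defines the risk by its cause, and the causes it lists are narrower than the risk. A bleeding tendency can also come from an anticoagulant or from a clotting disorder in which platelets are normal. Had the item stopped at the words for a bleeding tendency, it would have covered the disorders. The qualifier that follows limits it to platelet causes.

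What is at stake is the safety of the occasional participant. These are volunteers in an explanatory study, so there is no personal benefit to set against an avoidable bleed or bruise. The measurements and the comparison of before with after warm needling are not touched.

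**Working it through.** No figure in the plan depends on this point, so the check is mainly one of reading the text. The only arithmetic concerns exposure and the likely number affected.

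**Step 1. What the bleeding item covers.** The sentence can be read in two ways.

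| Reading | Excluded | Anticoagulant user named? | Non-platelet disorder named? |
|---|---|---|---|
| Three separate items | Bleeding tendency from thrombocytopenia; platelets below 20,000/µL; antiplatelet users | No | No |
| One item with three causes | Bleeding tendency, if caused by thrombocytopenia, low platelets or antiplatelet medicine | No | No |

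The gap is the same under both readings.

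**Step 2. Whether another criterion covers it.** The remaining exclusions in 2.2 are age below 20, pregnancy or breast-feeding, an empty stomach, and hypnotic or psychoactive medicines. None concerns clotting. Anticoagulants, coagulation disorders and a general bleeding-disorder exclusion are not mentioned elsewhere in the article. What remains is the word 'healthy', used in the abstract, in 2.1 and in 2.2, and not defined in any of them.

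**Step 3. Whether another safeguard covers it.** Section 2.7 has a measure specific to burns (the cardboard) and general measures (qualified doctors, limb points, the stopping rule). None is aimed at bleeding. The exclusion in 2.2 is therefore the only bleeding-specific safeguard in the document.

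**Step 4. Exposure.** 12 meridians × 2 acupoints = 24 acupoints per participant, all within one day. This measures exposure, not harm. Section 2.1 says that meridians are taken one at a time, so the 24 needles are not all in place together.

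**Step 5. Likely number affected.** The documents do not give the share of volunteers on an anticoagulant or with such a disorder, nor the share of them that 'healthy' would stop. Any figure for the chance of enrolling one would rest on assumption alone. A condition can be stated instead. If a share q of those enrolled were affected, the most likely count among n = 30 is the whole-number part of (n + 1)q = 31q. This is 0 for every q below 1/31 = 3.2%. So the most likely number is 0 of 30 unless more than about 3% of enrolled volunteers have one of these conditions after passing the 'healthy' criterion. I assume that the true share lies well below that among students and staff accepted as healthy.

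**The case against.** The strongest reply is that 'healthy' already does the work. It is the leading inclusion criterion. A clotting disorder is a disease, and an anticoagulant is ordinarily prescribed for a diagnosed condition, so neither person is a healthy volunteer in the usual sense. Most of this stands, and it is why the point is small. It does not close the gap. The word is undefined, staff as well as students are recruited, there is no upper age limit, and a person who feels well on long-term anticoagulation could reasonably be called healthy.

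Four stronger readings are tempting, and the documents do not support them.

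- A reader might infer that, because antiplatelet and psychoactive medicines are listed although participants must already be healthy, people not listed are meant to be admitted. The same list also repeats the age limit from the inclusion criteria, so repetition there shows little about intent.
- A reader might infer from the 20,000/µL figure that volunteers with moderately low platelets are let in. Thrombocytopenia is named beside it and 'healthy' stands above it, so the figure is redundant more than permissive. It is an editorial matter.
- A reader might infer that screening does not ask about clotting or medication. The article condenses a fuller protocol that is not shown, and screening procedure is detail that it may leave out. The point here is limited to the wording of a criterion that the article does state.
- A reader might infer a material risk of harm. Bleeding is listed as a minor effect, the needles are 0.3 mm in diameter, all points are on the limbs, and qualified doctors do the needling.

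**Conclusion.** The point holds as a minor safety wording matter, to be considered. The bleeding exclusion is drawn more narrowly than the risk it addresses, and 'healthy' covers most of the remainder but not certainly all of it.

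The number affected is most likely 0 of 30, and the expected harm is minor. That count is a judgement. It rests on the assumption that 'healthy' is applied in its ordinary sense and that few students and staff have these conditions; the documents give no figure for either. Sample size, power, outcomes, analysis and conclusions are unaffected.

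**What to change.** In 2.2, replace the bleeding item with:

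> known bleeding or clotting disorder (including thrombocytopenia), or current use of any antiplatelet or anticoagulant medicine

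This names the missing drug class and the non-platelet disorders. It also makes clear that medicine use excludes by itself, and it makes the 20,000/µL figure unnecessary.

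The cost is one reworded clause. The downside is that an occasional volunteer has to be replaced. Nothing in the design or analysis has to change.
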